*Pathogenic involvement of OSAS in cerebrovascular disease* is suggested by the direct relationship found between the severity of nocturnal oxygen desaturation and carotid intima-media thickness (IMT) and/or the occurrence of atherosclerotic plaques in the carotid arteries of OSAS patients, independent of hypertension (4, 54). Recently, two studies in patients with untreated PSG verified severe OSAS (14, 41), at low risk from the classical cardiovascular risk factors, have demonstrated the presence of early carotid atherosclerosis (increase in IMT). Thus, patients with severe OSAS appear more likely to develop early changes of cerebral macrovascular disease.

*We recently published a large cross-sectional study (29) in 110 heavy snorers (with only mild OSAS)*, with adequate power to assess associations between snoring and carotid vascular disease. The prevalence of carotid atherosclerotic plaque was 31%, with significant risk factors including age, male gender, hypertension, smoking history and heavy snoring. **The adjusted odds ratio for carotid atherosclerosis in the heavy snoring group (snoring greater than 50% sleep time) was substantially increased at 10.5 (2.1 – 51.8, 95% CI)**, and was clearly the strongest association. Importantly, this study is the first to demonstrate that snoring with mild OSAS (without nocturnal hypoxia) is a strong independent risk factor for carotid atherosclerosis. In support of this, the prevalence of carotid plaque in this study population was 1.8 times greater than that reported for the general population (27), and even higher than that seen in OSAS populations (41).

*The novelty and importance of this study by CIA and his team* were recognised by the publication of two separate editorial commentaries in the journal *Sleep* (16, 36), both of which concluded that the relationship between snoring and carotid atherosclerosis is an exciting and important new area of research to elucidate factors contributing to cardiovascular disease risk profiles. They noted that the significance of the finding may elevate the importance of snoring from a social annoyance to a vascular risk factor. If the independent association between snoring and carotid atherosclerosis

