**Subjects:** We will recruit 390 patients (130 patients/year) aged >45 years who are referred to the Westmead Hospital Sleep Laboratory for a routine diagnostic PSG for assessment of possible SDB. Exclusion criteria include past history of stroke, diabetes, atrial fibrillation, congestive cardiac failure, carotid artery surgery, and eye pathologies that preclude the measurement of retinal vessel calibre (e.g. age-related macular degeneration, glaucoma). Our Laboratory performs over 500 diagnostic PSG studies/year in this age group, with results demonstrating a Respiratory Disturbance Index (RDI) of <5 events/hr in 7% (normal controls), 5-15 events/hr in 24% (mild OSAS), 15-30 events/hr in 27% (moderate OSAS) and >30 events/hr in 42% (severe OSAS). Review of our

database indicates that 82% of target patients meet the inclusion criteria. We will stratify patient recruitment across the severity range. Allowing for a 50% participation refusal, there will be no problems recruiting target numbers.

**Baseline/Anthropometry Data:** We will record age, gender, body mass index, waist-hip ratio, and neck circumference. Questionnaire data will include cardiovascular risk (Framingham Questionnaire), Epworth Sleepiness Scale (ESS), snoring history, and smoking history. Detailed history of hypertension will include length of known diagnosis and current treatment. A fasting blood sample will be collected for lipid profile and glucose level.

**Procedures:** *PSG:* Sleep will be monitored using standard PSG procedures for our laboratory (29). In addition, we will record snoring sounds using a room sound level meter and quantify snore-related tissue vibration energy using an accelerometer attached to the skin surface of the neck.

*Carotid Artery Ultrasound:* Doppler ultrasound examination of both carotid arteries will be used to measure IMT (57) of the common carotid, plaque type and extent, lumen diameter, and peak systolic velocity.

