*Retinal Photography:* Each eye will be photographed following a standardized protocol using a high-resolution digital camera (Canon non-mydratic). Two colour retinal photographs will be taken from each eye, one centred on the optic disc (Diabetic Retinopathy Study [DRS] standard field 1) and another on the macula (DRS standard field 2) (13). Digital images will be graded for retinal microvascular lesions using standard protocols under direction of CIC. Qualitative signs will be recorded (see Background p3). The intra-grader reliability for detecting focal arteriolar narrowing and AV nicking is (kappa statistic) 0.80 and 0.87, respectively (57).

A computer-assisted grading method with high reproducibility will be used to measure the retinal vessel diameters and arteriole-to-venule ratio (AVR). Average retinal arteriolar or venular width (diameter) is calculated using the Parr-Hubbard formula (23, 45) and presented as the central retinal arteriolar equivalent (CRAE) or central retinal venular equivalent (CRVE). AVR can then be calculated from CRAE and CRVE. Intra- and inter-grader reliability of this method is high (51). Retinal emboli are intravascular lesions seen along the course of retinal arterioles, and may be present at a bifurcation. Detailed methods of grading retinal abnormalities have been described (57).

**Protocol:** Subjects will undergo an overnight PSG study. Carotid ultrasound, retinal photography and supine blood pressure will be performed at ~2000hrs and repeated at ~0600hrs. A major outcome focuses on overnight change in measurements, where subjects act as their own controls.

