**Statistical Analysis and Sample Size:** Univariate relationships between measures of OSAS or snoring severity (AHI, Arousal Index, Oxygen Desaturation Index, snore index) [independent variables], and overnight change in CRAE, CRVE, AVR and IMT [dependent variables], will be examined using linear regression analysis for continuous data and  $X^2$  analysis for categorical data. Stepwise multiple linear regression or logistic regression will be used to examine associations of OSAS and snoring (continuous data) with dependent variables, including any interactions with anthropometric and vascular risk factor data. From our preliminary data, a sample size of 384 for the cohort study will have 80% power to detect a difference in the CRVE means of 8.0  $\mu\text{m}$  (and difference in CRAE means of 13.6  $\mu\text{m}$ ), assuming that the common standard deviation is 24.1  $\mu\text{m}$  for CRVE and 13.6  $\mu\text{m}$  for CRAE, using a two group t-test with two sided significance of  $p=0.017$ . For the overnight changes, a sample size of 146 will have 80% power to detect a correlation coefficient of 0.25 between AVR and snoring using linear regression, assuming normal distribution of AVR and a two sided significance level of  $p=0.025$ . Power estimates are conservative based on the dependent variables with the smallest detected signals from our preliminary retinal data.

**Outcomes:** This study will establish the relationship between snoring / OSAS and the presence of cerebral microvascular and macrovascular disease in a cross section of subjects. Overnight changes in the retinal vessel calibre will demonstrate for the first time a mechanism by which SDB acutely and adversely affects the microvasculature. In addition, if the cross-sectional analysis of subjects

demonstrates the same changes in vessels as a function of SDB severity, then this would support these changes becoming chronic over time. Finally, we will examine for the presence of retinal emboli before and after sleep, which will provide the first evidence for snoring and OSAS being associated with active plaque disease, with potential for plaque disruption and embolic stroke.

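### Project 1 commits to stepwise regression over four related sleep measures, with no primary exposure and no confounder kept in by rule

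*Protocol*

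**What the plan says.** The statistics paragraph of Project 1 (Protocol, Project 1, Statistical Analysis and Sample Size) first sets up univariate analyses. The predictors are "measures of OSAS or snoring severity (AHI, Arousal Index, Oxygen Desaturation Index, snore index) [independent variables" and the outcomes are "overnight change in CRAE, CRVE, AVR and IMT [dependent variables". It then names the multivariable method: "Stepwise multiple linear regression or logistic regression will be used to examine associations of OSAS and snoring (continuous data) with dependent variables". Anthropometric and vascular risk factors enter that sentence only through the phrase "including any interactions with anthropometric and vascular risk factor data".

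The paragraph names no primary sleep measure, lists no covariate that stays in regardless of its p-value, and gives no entry or removal threshold. Two significance levels appear, 0.017 and 0.025, both inside the power statements.

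Three other places bear on the point:
- The Baseline/Anthropometry paragraph says "We will record age, gender, body mass index, waist-hip ratio, and neck circumference", and goes on to smoking, hypertension history, lipids and glucose. The likely confounders are therefore collected.
- The Protocol paragraph of Project 1 says "A major outcome focuses on overnight change in measurements, where subjects act as their own controls".
- The Background reports, from the group's earlier carotid plaque study, "significant risk factors including age, male gender, hypertension, smoking history and heavy snoring".

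**The concern.** Project 1 is observational. Its first research question compares baseline vascular disease between patients with heavy snoring and OSAS and those with mild or no disease. The group's own earlier work found age, sex, hypertension and smoking to be risk factors for carotid plaque, so the comparison is only as good as its adjustment for such factors.

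Stepwise selection lets p-values decide which of four related severity measures survives and which confounders survive, with interactions as further candidates. Two harms follow. The p-values and intervals of the surviving terms are computed as if the model had been fixed in advance. And a confounder that narrowly misses entry is left out, so its effect can be credited to a sleep measure. The Background separates hypoxia, blood pressure surges and snoring vibration as possible mechanisms, so which index survives will be read as evidence about mechanism.

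**Working it through.** **1. The plan's own figures.**
- Cohort comparison: n per group = 2(z₀.₉₉₁₅ + z₀.₈₀)² × 24.1² / 8.0² = 190, or 380 in total, against 384 stated. At 192 per group, power is 80.3% (noncentral t).
- Overnight correlation: n = [(z₀.₉₈₇₅ + z₀.₈₀) / atanh(0.25)]² + 3 = 148.7, against 146 stated. Without the +3 it is 145.7, which rounds up to 146.

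Both reproduce. Each alpha belongs to a single test (a two-group t-test; one correlation of AVR with snoring). The protocol states no error rate for the stepwise models.

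**2. Inputs.** From the protocol: four sleep measures, four overnight-change outcomes, and sample sizes of 146, 384 and 390. Assumed, because not given: correlations among the measures, selection thresholds, the candidate list and the strength of confounding. All simulations use linear models and one outcome.

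**3. Four measures, before any covariate selection.** With independent null measures, P(at least one p < 0.05) = 1 − 0.95⁴ = 18.5%. With equal correlation among them (1,000,000 draws):

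| Correlation | P(at least one) | Multiple of 5% |
|---|---|---|
| 0 | 18.6% | 3.7 |
| 0.3 | 17.4% | 3.5 |
| 0.5 | 15.6% | 3.1 |
| 0.7 | 13.0% | 2.6 |
| 0.9 | 9.3% | 1.9 |

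**4. Separating selection from multiplicity.** Simulation at n = 390 with no true sleep effect. Assumed: AHI, arousal and desaturation correlate 0.8, snoring 0.4 with them, and exposures 0.35 with BMI and blood pressure; seven covariates. The last column divides by 5%.

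| Analysis | At least one null sleep measure at 0.05 | Multiple |
|---|---|---|
| Forward stepwise | 11–19% | 2.2–3.8 |
| Backward elimination | 18–24% | 3.6–4.8 |
| Full model, four measures, no selection | 15–17% | 3.0–3.4 |
| Four separate adjusted models | 14–16% | 2.8–3.2 |
| One exposure, covariates forced in | 4–6% | 0.8–1.2 |

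Forward selection is about level with the unselected four-measure analyses; backward elimination is above them. All three true confounders were kept in anything from 10% to 90% of runs as their assumed standardised effect rose from 0.10 to 0.20.

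**5. When confounders are dropped.** Forward stepwise (entry 0.05, removal 0.10), sleep measures correlated 0.6, eight covariates of which three are true confounders. 600 runs per row, so the Monte Carlo standard error is about √(0.2 × 0.8 / 600) = 1.6 percentage points at a rate of 20%. *Effect* is the standardised effect of each confounder; *r* is the correlation of their composite with the sleep measures. A to D give the percentage of runs with at least one false sleep association: A, stepwise on everything; B, covariates forced in and selection only among sleep measures; C, full model without selection; D, one pre-specified exposure, covariates forced in. E is the percentage in which stepwise lost at least one true confounder.

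| n | Effect | r | A | B | C | D | E |
|---|---|---|---|---|---|---|---|
| 146 | 0.1 | 0.4 | 18.2 | 11.8 | 16.0 | 3.5 | 98.7 |
| 146 | 0.1 | 0.6 | 29.3 | 13.8 | 17.3 | 4.8 | 99.2 |
| 146 | 0.2 | 0.4 | 25.2 | 15.0 | 17.0 | 5.5 | 75.0 |
| 146 | 0.2 | 0.6 | 41.8 | 16.3 | 16.5 | 5.0 | 85.8 |
| 384 | 0.1 | 0.4 | 21.7 | 13.8 | 15.7 | 4.8 | 89.2 |
| 384 | 0.1 | 0.6 | 40.5 | 16.8 | 18.3 | 5.3 | 93.3 |
| 384 | 0.2 | 0.4 | 19.5 | 16.8 | 17.3 | 6.2 | 11.5 |
| 384 | 0.2 | 0.6 | 25.5 | 13.3 | 15.0 | 3.8 | 17.0 |

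A minus B isolates the harm from letting confounders drop out. It runs from 2.7 points (19.5 − 16.8) to 25.5 points (41.8 − 16.3). B is no higher than C in any row, so forward selection among the sleep measures alone adds nothing beyond testing all four.

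**The case against.** The strongest reply is about attribution. Comparing stepwise on four measures with a single pre-specified exposure mixes selection with multiplicity, and most of the gap is multiplicity: a full model without any selection gives 15–17%. That stands. Merely deleting the word stepwise while still testing four measures at 0.05 would leave most of the excess in place.

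Second, every size rests on inputs the protocol does not give. That also stands, and confounder loss is especially sensitive: at n = 384 it falls from about nine runs in ten to between one and two in ten when the assumed effect doubles.

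Third, the outcomes listed for the regression are overnight changes with each patient as his or her own control, so stable patient factors partly cancel. That stands in part. Such factors can still relate to the size of the change, and the first research question is a comparison between patients, where nothing cancels.

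Fourth, forced terms, thresholds and multiplicity rules often sit in a statistical analysis plan, and stepwise does not exclude forced terms. This does not remove the point. The protocol itself fixes a data-driven method, so the issue is the method chosen and not a missing detail.

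**Conclusion.** The point holds. The protocol fixes stepwise regression over four related exposures with no primary one and no protected confounder, and a better method is available on data already planned. For one outcome and no true sleep effect, false retention at 0.05 is about two to four times nominal. Most of this comes from testing four measures without a primary one. Selection adds to it mainly under backward elimination (18–24%) or when real confounders are dropped (18–42% in the settings tried). These ranges depend on the assumed correlations, thresholds and confounder effects.

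A reader might infer more than the documents support:
- That stepwise selection by itself triples or quadruples false associations. Unselected analyses of the same four measures give nearly the same rate as forward selection.
- That the stated levels of 0.017 and 0.025 are breached. They belong to the power statements and are not tied to these models.
- That key confounders will nearly always be lost. That holds only if their effects are weak.
- That the overnight-change results are as exposed to confounding as the cross-sectional ones. The own-control design argues against this.
- That the mechanism the selection points to is arbitrary. How often it picks the wrong index was not calculated.

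**What to change.** Replace stepwise selection by models written down in advance:
- **Primary exposure per question.** For overnight change, the snore index, on which that analysis is powered. For the cross-sectional question, AHI or RDI; the protocol uses RDI for its severity bands and AHI in the statistics paragraph, so name one.
- **Covariates.** Force in age, sex, BMI, smoking and lipids, with no selection.
- **Blood pressure.** Show each model with and without blood pressure or hypertension. The Background lists blood pressure swings and surges among the possible mechanisms, so adjusting for it may remove part of the effect under study.
- **Other sleep indices and interactions.** Fit them in separate models labelled secondary.
- **Multiplicity.** State an adjustment across exposures and outcomes. As a guide, testing four measures at 0.05/4 = 0.0125 each holds the error for one outcome at 4.9% if they are independent and 2.6% if they correlate 0.9. With four outcomes there are 4 × 4 = 16 exposure–outcome pairs, so the rule must cover outcomes too.

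With one exposure and forced covariates, the false-positive rate per outcome was 3.5–6.2% in the confounded settings above. The change needs only protocol or analysis-plan wording. The covariates are already collected, and 390 patients support about eight terms. The price is slightly wider intervals and a few more models to report.

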## RESEARCH PLAN:

### PROJECT 1: The Influence of Untreated Snoring and OSAS on Cerebral Vascular Disease.

**Hypotheses:** 1) Patients with untreated heavy snoring and OSAS will demonstrate an increased prevalence of retinal microvascular and carotid macrovascular abnormalities.

2) Microvascular and macrovascular abnormalities will increase over a night of sleep, with the overnight increase correlating with the severity of the snoring and OSAS.

3) Patients with untreated heavy snoring and OSAS, and with established carotid atherosclerotic plaque, will demonstrate an increased incidence of overnight retinal arteriolar emboli (compared with normal controls), consistent with active carotid plaque disease.

**We propose to address the above hypotheses by comparing pre and post sleep data in patients with untreated heavy snoring and OSAS and comparing any differences to those with mild or no snoring and OSAS, to directly address the following specific research questions:**

- 1) Do patients with heavy snoring and OSAS demonstrate an increased baseline prevalence of microvascular disease (retinal vessel changes) and/or macrovascular disease (carotid artery IMT)?
- 2) Do patients with OSAS demonstrate a decrease in arteriolar diameter or an increase in retinal venular diameter following overnight sleep as a function of the severity of their OSAS or snoring?
- 3) Do patients with heavy snoring and OSAS, and with carotid atherosclerotic plaque, demonstrate a higher frequency of prevalent and overnight incident retinal arteriolar emboli?

**Design:** Nested case-control cohort study in snoring and OSAS referrals, comparing severe cases with control/mild cases (see below) at baseline and for overnight changes in vascular abnormalities.

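### Project 1's 80% power for the cross-sectional CRVE comparison fits two equal groups that use the whole cohort, not the severe versus control/mild contrast in the Design

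*Protocol*

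**What the plan says.** All references are to Project 1 in the protocol.

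- **Design.** The study is a nested case-control cohort, "comparing severe cases with control/mild cases (see below) at baseline and for overnight changes in vascular abnormalities".
- **Enrolment, under the Subjects heading.** The target reads: "We will recruit 390 patients (130 patients/year) aged >45 years". The laboratory's studies are divided into four RDI classes: below 5 (normal controls, 7%), 5-15 (mild, 24%), "15-30 events/hr in 27% (moderate OSAS"), and above 30 (severe, 42%). On how enrolment is spread it says: "We will stratify patient recruitment across the severity range". No stratum sizes are given.
- **Statistical Analysis and Sample Size.** "a sample size of 384 for the cohort study will have 80% power to detect a difference in the CRVE means", with that difference set at 8.0 µm, "assuming that the common standard deviation is 24.1" µm, by a two-group t-test at two-sided 0.017. The paragraph does not say which patients form the two groups or in what ratio.
- **Preliminary Data (Background).** The pilot, from which the power inputs are said to come, treats RDI below 15 as control.

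**The concern.** A two-group power calculation counts only patients who belong to one of the two groups. The 384 in the calculation is almost the full 390, so it leaves no room for a third class. Yet the stated contrast names severe on one side and control/mild on the other, and the protocol enrols a moderate class that is in neither. Each moderate patient enrolled adds to the total without adding to the test.

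This is the only power statement for the cross-sectional retinal comparison (hypothesis 1, research question 1). If the true power is near 60-65%, the chance of missing the planned 8.0 µm difference is about 36-39% rather than 20%. A null result could then be read as better supported than it is, particularly as the same paragraph calls its power estimates conservative.

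**Working it through.** **Inputs.** From the sample-size paragraph: difference 8.0 µm, SD 24.1 µm, two-sided alpha 0.017, power 80%, N = 384. From Subjects: 390 recruited; class shares 7%, 24%, 27% and 42%. Not stated, so assumed below: the group definitions and the stratum sizes.

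**Step 1: reproduce 384.** By the normal approximation, n per group = 2 × [(z for 1 − 0.017/2 + z for 0.80) × SD / difference]² = 2 × [(2.387 + 0.842) × 24.1 / 8.0]² = 189.2, so 190. The noncentral t gives 191 per group at 0.017, and 192 per group (384 in total) at 0.05/3. With 192 v 192 at 0.017, power is 80.3%. The stated figure is therefore correct for two equal groups, and those groups use the whole sample.

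**Step 2: group sizes under other definitions, 390 recruited.**

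- Control/mild at the laboratory mix: 390 × 0.31 = 121. Severe: 390 × 0.42 = 164. Moderate, in neither group: 390 × 0.27 = 105.
- Equal thirds (control/mild, moderate, severe): 130 v 130.
- Four equal RDI strata: about 97 severe v 195 control/mild.
- Moderate counted as cases (RDI of 15 or more v below 15): 390 × 0.69 = 269 v 121.
- Moderate counted with control/mild: 390 × 0.58 = 226 v 164.

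**Step 3: power and detectable difference.** SE = 24.1 × √(1/n1 + 1/n2). The noncentrality is 8.0/SE, and power comes from the noncentral t with n1 + n2 − 2 degrees of freedom. For 164 v 121: SE = 24.1 × √(1/164 + 1/121) = 2.888 and noncentrality = 2.77.

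| Groups compared | n1 v n2 | Power for 8.0 µm | Difference detectable with 80% power |
|---|---|---|---|
| Implied by 384 | 192 v 192 | 80.3% | 8.0 µm |
| Severe v control/mild, laboratory mix | 164 v 121 | 64.4% | 9.4 µm |
| Severe v control/mild, equal thirds | 130 v 130 | 60.8% | 9.7 µm |
| Severe v control/mild, four equal strata | 97 v 195 | 60.7% | 9.7 µm |
| RDI of 15 or more v below 15 | 269 v 121 | 73.7% | 8.55 µm |
| Severe v all others | 164 v 226 | 79.9% | 8.0 µm |

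**Step 4: can stratified recruitment restore 80%?** Only by enrolling about 192 severe and 192 control/mild patients. That leaves 390 − 384 = 6 places for moderate patients, which does not fit recruitment across the severity range.

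**Step 5: the overnight calculation.** It uses a correlation of 0.25, n = 146 and alpha 0.025. By Fisher's z, 0.2554 × √143 − 2.241 = 0.813, or about 79% power. It needs no two-group split, so the moderate class does not affect it.

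**The case against.** The strongest objection is that the low figures rest on one reading. The sample-size paragraph never names its groups. The research questions speak of heavy snoring as well as OSAS, so a heavy snorer with moderate RDI is not plainly outside both groups. The pilot's RDI cut at 15 leaves nobody out and gives about 74%. Grouping moderate with control/mild gives about 80%. A split at 50% snoring time would, if the cohort resembles the pilot (49.4 ± 26.2%, roughly normal), divide it about 191 v 199 and give about 81%. The laboratory mix is also not the stated recruitment plan, and the equal-strata scenarios are illustrations.

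Much of this stands: 61-64% is conditional and should not be reported as the study's established power. It does not rescue the 80%, however. The Design line contrasts severe with control/mild, and the only classes defined below it are the RDI classes, with moderate kept separate. The pilot's cut still falls short. Placing moderate with control/mild goes against the Design's wording, and nothing ties the t-test to a snoring split.

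Some stronger readings are tempting but not supported:

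- A reader might infer that Project 1 as a whole is underpowered. The overnight analysis, which the Protocol subsection calls a major outcome, has its own calculation.
- A reader might infer that regression on continuous severity in the same paragraph already covers this comparison. The univariate regression there takes overnight change as the outcome, not baseline calibre.
- A reader might infer that too few control/mild patients exist to fill a group of 192. The laboratory figure of over 500 studies a year is a floor, so no ceiling follows from it.
- A reader might infer that RDI cannot be known at recruitment. The protocol does not say so.

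**Conclusion.** The point holds in a limited form. The stated 80% is correct for two equal groups of about 192, but it does not match the contrast written in the Design. Taking that contrast literally, power for an 8.0 µm CRVE difference is about 64% at the laboratory mix or about 61% with equal strata, and the detectable difference is about 9.4 to 9.7 µm. Counting all patients with RDI of 15 or more as cases gives about 74% and about 8.55 µm.

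Which figure applies depends on group definitions and stratum sizes that the protocol does not state. All figures assume 390 analysable patients, the protocol's SD of 24.1 µm and alpha of 0.017. The finding is confined to the cross-sectional CRVE power statement. It is a misstated precision, not a source of bias or of risk to participants, and it does not touch Project 2.

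**What to change.** 1. In Design and Subjects, define the two groups by explicit criteria, say where moderate patients (RDI 15-30) go, and give the planned number in each stratum.
2. In Statistical Analysis and Sample Size, restate the CRVE figure for that contrast. For severe versus control/mild at the laboratory mix, for example: 390 recruited, 164 v 121 compared, about 64% power for 8.0 µm, or 80% power for 9.4 µm, at two-sided 0.017.
3. Optionally, add a regression of baseline CRVE and CRAE on continuous severity in all 390 patients, so that moderate patients contribute. It has 80% power for a correlation of tanh(3.228/√387) = 0.163, about 0.16, at two-sided 0.017. Write it as a new analysis, because the univariate regression now in the section has overnight change as its outcome. A correlation of 0.16 is not by itself equivalent to an 8.0 µm group difference, so the two should be reported separately.

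The cost is protocol wording and a less favourable stated power. No additional patients or measurements are needed, and the overnight calculation stays as it is.
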